### Study enrolment

All patients who previously gave informed consent in two national registries, for dialysis patients (RENINE) and kidney transplant recipients (NOTR), are selected for enrolment. Patients with CKD stages G4-G5 will be enrolled from a cohort of non-university hospitals (Santeon). All patients eligible to the registry will be followed to assess incidence of COVID-19 after vaccination, (S)AEs and vaccination status. Data of non-vaccinated patients which will be derived from RENINE and NOTR registries serve as control. Furthermore, data on vaccination efficacy in the general population, which will be derived from the National Institute for Public Health and the Environment (RIVM), serve as a control group.

For measurement of antibodies after completion of SARS-CoV-2 vaccination we intend to include a random subset of patients with CKD stages G4-G5 (*n* = 4000), patients on dialysis (*n* = 4000), and patients after kidney transplantation (*n* = 4000) (Fig. 2). Patients older than 80 years are excluded from participation because they had priority in the Dutch national vaccination scheme over other high-risk groups. Consequently, they were vaccinated longer than 28 days ago, which is the accepted term in wherein finger-prick tests are obtained for antibody measurement.

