### Outcome definitions

For an overview of the clinical endpoints in this study we refer to Table 3.

**Table 3 Tab3:** Clinical endpoints LESS-CoV-2 study

*Primary endpoint*	
Incidence (per person-year) of COVID-19 in a two-years period after SARS-CoV-2 vaccination in patients with CKD stage G4-G5 or on KRT.	
*Secondary endpoints*	
Efficacy	
• The antibody based immune response to SARS-CoV-2 vaccination at 28 days after SARS-CoV-2 vaccination.	
• The durability of the antibody response at 6 months after SARS-CoV-2 vaccination	
Safety	
• Incidence of mortality	
• Incidence of AEs of specific interest as defined by (inter) national authorities	
• Incidence of a combined endpoint of acute rejection or graft failure in kidney transplant recipients	
• Incidence of HLA antibodies defined as cPRA > 5% in dialysis patients on the waiting list for their first kidney transplantation	
*Exploratory endpoints*	
Vaccination coverage rates	
Disease severity in patients who develop COVID-19, assessed as	
• Hospitalization	
• ICU admission	
• Mechanical ventilation	
PROMs in patients on dialysis	
SARS-CoV2 genotype in patients with COVID-19 (in case available)	

*COVID-19* Coronavirus Disease 2019, *SARS-CoV-2* Severe Acute Respiratory Syndrome Coronavirus-2, *CKD* Chronic Kidney Disease, *KRT* Kidney Replacement Therapy, *AEs* Adverse Events, *HLA* Human Leukocyte Antigen, *cPRA* Calculated Panel Reactive Antibody, *ICU* Intensive Care Unit, *PROMs* Patient Reported Outcome Measures

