#### Analysis of primary endpoint

Incidence rates of COVID-19 within 2 years after vaccination will be reported for each study population separately and incidence rates will be compared. Primary comparisons are comparisons of COVID-19 incidence rates in vaccinated patients versus non-vaccinated patients and versus the vaccinated general population. These comparisons will be made separately for patients with CKD stages G4-G5 or on KRT. For comparison of incidence rates, we will calculate crude hazard ratios. Vaccine efficacy will be reported as 100 × (1- hazard ratio). We will calculate model adjusted hazard ratios using multivariable Cox-regression, in case of imbalance in study populations regarding relevant characteristics, such as age, sex, comorbidity, kidney replacement modality and use of immunosuppressive agents. Cause specific hazard ratios will be estimated to account for competing risk of mortality. Starting date of follow-up will be the date of second vaccination in vaccinated patients. Starting date of follow-up in non-vaccinated patients will be the same date (or +/− 7 days from date of vaccination) as date of vaccination in the matched vaccinated patients to account for changes in incidence of COVID-19 over time. Non-vaccinated patients will be censored at the day of vaccination in case they are vaccinated before the end of follow-up. The aforementioned analyses will be repeated in patients with and patients without evidence of prior infection. Among vaccinated patients, incidence rates will also be compared across the various vaccines that will be used. For this purpose, vaccinated patients with CKD stages G4-G5 or on KRT and general population again will be analysed separately.

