#### Analysis of secondary endpoints

##### Efficacy - Antibody response

Participants will be classified as responders or non-responders [17]. Number and proportion of responders and non-responders at day 28 will be reported for each patient population. Pearson chi-2 test will be performed to assess whether antibody response differ between patient groups. In subsequent sensitivity analyses we will perform multiple regression analyses correcting for possible differences in age and sex between the patient groups. Additionally, in kidney transplant recipients we will investigate whether time after transplantation, and the different immunosuppressive regimens are associated with response rate.

To assess durability of response within each patient group, we will report and compare response at day 28 with response at month 6 after vaccination. Comparison will be made using McNemar test.

The association between antibody response after SARS-CoV-2 vaccination and protection against COVID-19 will be examined for each patient group separately. For this, we will compare the antibody response at 28 days after vaccination in patients who develop COVID-19 with the antibody response in patients who did not develop COVID-19. Similar comparison will be made at 6 months after vaccination. We will examine this by use of the t-test or if more appropriate a non-parametric test. Subsequently, in a logistic regression model using Youden’s index, a cut-off in the antibody response at 28 days will be defined to serve as a correlate of protection against COVID-19.

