## Discussion

In the LESS-CoV-2 study we will assess the efficacy and safety of the mRNA-1273, BNT162b2, ChAdOx1 nCoV-19 and Ad26.COV2.S SARS-CoV-2 vaccines in Dutch patients with CKD stages G4-G5, on dialysis or after kidney transplantation.

We expect to determine an antibody response cut-off value which allows to predict protection against COVID-19 breakthrough infection after completion of SARS-CoV-2 vaccination. This contributes to the establishment of surrogate endpoints which will facilitate the development and approval of new vaccines [18]. In this study, we will identify non-responders by means of an insufficient antibody response after SARS-CoV-2 vaccination. This population can be offered a booster vaccine or an alternative vaccine to assess whether or not a sufficient antibody response can still be achieved.

Furthermore, we will address the safety of SARS-CoV-2-vaccination in patients with severe kidney insufficiency and in those that are treated with immunosuppressive drugs. Since these patients were not sufficiently represented in the large registration studies of the various vaccines, specific AEs associated with kidney failure and its treatment may not have been recognized so far. In addition, rare but possibly harmful AEs must be searched for in pharmacovigilance studies after widespread distribution of the vaccines. Recent reporting of vaccine-induced immune thrombotic thrombocytopenia caused by the ChAdOx1 nCoV-19 and Ad26.COV2.S SARS-CoV-2 vaccines is a possible example of such a rare complication [19]. It is essential to collaborate with large registry studies to be able to detect rare SAEs in patients with kidney disease. Different SARS-CoV-2 vaccines are administered to our subjects, and for that reason we will monitor the development of immunisation against HLA-antigens, allograft rejection and/or kidney transplant failure following SARS-CoV-2 vaccination.

Considering that items such as mental QoL, anxiety and depression may be positively influenced by vaccination, it is highly relevant to monitor the effect of SARS-CoV-2 vaccination on patient reported outcome measurements (PROMs). In our cohort of dialysis patients PROMs have been monitored since 2019. During the study we will further monitor the course of mental health of vaccinated and non-vaccinated dialysis patients and compare this to pre-COVID-19 pandemic era and the COVID-19 pandemic era without vaccines.

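### The day-28 Youden cut-off measures discrimination among vaccinated patients, not protection, so it cannot by itself serve as a correlate of protection.

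*Protocol article*

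**What the plan says.** The Protocol article, under Efficacy - Antibody response, compares the day-28 antibody response "in patients who develop COVID-19 with the antibody response in patients who did not develop COVID-19", with a similar comparison at 6 months. The association "will be examined for each patient group separately". The step that follows fits a logistic model and applies Youden's index, with this aim: "a cut-off in the antibody response at 28 days will be defined to serve as a correlate of protection against COVID-19". Model, selection rule, sampling time and purpose are therefore all fixed in the text.

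The Discussion attaches weight to the result: "We expect to determine an antibody response cut-off value which allows to predict protection against COVID-19 breakthrough infection". It adds that this contributes to establishing surrogate endpoints for the development and approval of new vaccines.

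Protection has its own definition under Analysis of primary endpoint: "Vaccine efficacy will be reported as 100 × (1- hazard ratio"), with non-vaccinated patients as one comparator. That section uses Cox regression and cause-specific hazards because of competing mortality. It also aligns start dates of non-vaccinated and matched vaccinated patients because incidence changes over time. Nothing there links the efficacy measure to titre.

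**The concern.** A correlate of protection should say how much a given titre lowers the risk of infection. Youden's index answers another question: which titre best separates cases from non-cases when sensitivity and specificity count equally. It returns a single value even when risk falls smoothly and no boundary exists.

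The outcome model adds a second problem. A yes/no outcome treats a patient who died early without COVID-19 like one followed for the full period, and an infection in a quiet month like one in a wave. The primary endpoint covers "Incidence (per person-year) of COVID-19 in a two-years period after SARS-CoV-2 vaccination", and the plan itself measures titre again at month 6 to study durability.

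At stake is how the result is read. Patients above the line could be taken as protected and those below as unprotected, and the value could be carried into work on surrogate endpoints.

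**Working it through.** **Inputs.** From Study enrolment: "patients with CKD stages G4-G5 (*n* = 4000), patients on dialysis (*n* = 4000"), and the same number after kidney transplantation, so n = 4,000 per group. The article gives no incidence, association strength or unvaccinated risk. These are assumptions, shown as ranges. There is no plan figure to reproduce for this step.

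**1. Where the Youden point falls.** Let r(x) be the risk at titre x, decreasing in x, p the cohort average risk and f(x) the titre density. The densities are f(x)·r(x)/p in cases and f(x)·(1 − r(x))/(1 − p) in non-cases. J(c) is the proportion of cases at or below c minus the proportion of non-cases at or below c. It is maximal where the two densities are equal:

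r(c)/p = (1 − r(c))/(1 − p), hence r(c) = p.

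Numerical check with standard normal log titre and odds ratio (OR) 0.65 per SD:

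| Incidence | Cut-off (SD) | Risk at cut-off |
|---|---|---|
| 1% | −0.21 | 1.0% |
| 3% | −0.20 | 3.0% |
| 10% | −0.17 | 10.0% |
| 30% | −0.08 | 30.0% |

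The cut-off barely moves while the risk at it rises thirtyfold.

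**2. What it says about protection.** Take 10% incidence and OR 0.65 per SD. Risk is 13.52% below the cut-off, 10.0% at it and 7.32% above it. Check: 43.25% of patients lie below −0.17 SD, and 0.4325 × 13.52% + 0.5675 × 7.32% = 10.0%. With efficacy approximated as 100 × (1 − risk ratio):

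| Assumed unvaccinated risk | Efficacy below | At cut-off | Above |
|---|---|---|---|
| 10% | −35% | 0% | 27% |
| 15% | 10% | 33% | 51% |
| 20% | 32% | 50% | 63% |
| 40% | 66% | 75% | 82% |

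The cut-off is the same in all four rows, because unvaccinated risk never enters its calculation.

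**3. No association.** With OR 1.0, a cut-off is still returned. Over the assumed incidences, the 95% range runs from about the 2nd to the 99th titre percentile.

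**4. Precision.** Simulation with n = 4,000, normal log titre and smooth risk with no true threshold; 95% range of the chosen cut-off:

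| Incidence (cases) | Association per SD | Range (percentiles) |
|---|---|---|
| 1% (40) | OR 0.65 | 12th–75th |
| 3% (120) | HR 0.8 | 13th–79th |
| 3% (120) | OR 0.65 | 18th–68th |
| 10% (400) | HR 0.6 | 25th–58th |
| 30% (1,200) | HR 0.6 | 33rd–56th |

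More cases narrow the range but do not turn the point into a boundary. At 30% incidence and HR 0.6, risk is still 21% above the optimum, against 41% below.

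**5. Outcome models side by side.** The primary analysis uses Cox regression, cause-specific hazards and aligned start dates. The cut-off step, as stated, is a logistic model of COVID-19 yes or no. The reasons given for the former apply equally to the latter.

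**The case against.** Several points on the other side stand.

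- **Sampling noise.** A reader might infer that the cut-off would be mainly noise. The article does not support that, since it gives neither case count nor association strength. At 10% incidence and HR 0.6, apparent J is 0.226 against 0.206 true, with a best achievable 0.211. Even at 3% and HR 0.8, true J at the chosen point (0.081) is close to the best possible (0.090). The cut-off wanders largely because J is flat near its maximum. A two-component titre distribution (assumed 40/60) narrows the range to the 34th–50th percentile at 10% and HR 0.6. At 3% and HR 0.8 the range stays wide, 17th–74th.
- **Non-responders.** A reader might infer that this cut-off will identify them. The article classifies responders by a cited source before the Youden step, and the Discussion speaks only of an insufficient response without naming this value.
- **Surrogate endpoint.** The Discussion says the cut-off contributes to establishing surrogates, not that it will itself be one.
- **Internal validation and intervals.** These may be in the full protocol or analysis plan, which are not shown. Their absence from a condensed article is no finding.
- **Reach.** No correlate or cut-off is listed in Table 3, and the primary analysis is unaffected. Antibody levels are also compared at both day 28 and month 6, so the cut-off is not the only look at the association.

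None of this alters what the index measures. Validation would correct apparent performance, but it would not bring unvaccinated risk into the cut-off.

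**Conclusion.** The point holds in a limited form. The stated rule yields a discriminating cut-off among vaccinated patients and does not measure protection as the article defines it. That r(c) = p requires only a risk that falls smoothly with a single marker. The 0% to 75% spread in efficacy rests on the assumed unvaccinated risks and on a risk ratio standing in for the hazard ratio.

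The yes/no outcome is a weaker choice than the article's own primary analysis. How much is lost through unequal follow-up or death cannot be judged, because no outcome window is given for the logistic model.

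Imprecision is possible but conditional: wide with few cases or a weak association, moderate with 400 or more cases and a strong one. Inflation of J likewise falls from 0.083 with 40 cases to 0.022 with 400 at OR 0.65, and it concerns apparent performance more than the titre value. This is a matter for a secondary analysis and should be changed because of the use the Discussion foresees.

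**What to change.** Under Efficacy - Antibody response, replace the logistic/Youden step by a cause-specific Cox model in each patient group, with:

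- log anti-RBD IgG as a continuous spline term;
- follow-up from the sample date, so that the titre precedes the events;
- calendar time accounted for;
- adjustment for age and immunosuppression;
- the month-6 titre as an updated value.

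Report the risk curve over titre with confidence bands.

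If one threshold is still wanted, define it as the titre giving a pre-specified hazard reduction versus non-vaccinated patients, with a bootstrap interval. State that this comparison is non-randomised. Restrict it to groups that have such controls: Study enrolment names RENINE and NOTR as their source (dialysis and transplantation), but none for CKD stages G4-G5.

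Otherwise, describe the Youden value only as a cut-off that discriminates cases from non-cases, and soften the Discussion to match.

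The antibody and event data are already planned, so the curve costs only analysis wording. The downside is that the result may be a curve rather than one number. A threshold for CKD stages G4-G5 would also need a source of non-vaccinated controls.

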##### Safety

Incidence rates of (S)AEs, mortality, acute rejection, graft failure or HLA antibodies will be calculated and compared across patient groups in analyses similar to analysis of the primary outcome.

## Discussion

In the LESS-CoV-2 study we will assess the efficacy and safety of the mRNA-1273, BNT162b2, ChAdOx1 nCoV-19 and Ad26.COV2.S SARS-CoV-2 vaccines in Dutch patients with CKD stages G4-G5, on dialysis or after kidney transplantation.

We expect to determine an antibody response cut-off value which allows to predict protection against COVID-19 breakthrough infection after completion of SARS-CoV-2 vaccination. This contributes to the establishment of surrogate endpoints which will facilitate the development and approval of new vaccines [18]. In this study, we will identify non-responders by means of an insufficient antibody response after SARS-CoV-2 vaccination. This population can be offered a booster vaccine or an alternative vaccine to assess whether or not a sufficient antibody response can still be achieved.

Furthermore, we will address the safety of SARS-CoV-2-vaccination in patients with severe kidney insufficiency and in those that are treated with immunosuppressive drugs. Since these patients were not sufficiently represented in the large registration studies of the various vaccines, specific AEs associated with kidney failure and its treatment may not have been recognized so far. In addition, rare but possibly harmful AEs must be searched for in pharmacovigilance studies after widespread distribution of the vaccines. Recent reporting of vaccine-induced immune thrombotic thrombocytopenia caused by the ChAdOx1 nCoV-19 and Ad26.COV2.S SARS-CoV-2 vaccines is a possible example of such a rare complication [19]. It is essential to collaborate with large registry studies to be able to detect rare SAEs in patients with kidney disease. Different SARS-CoV-2 vaccines are administered to our subjects, and for that reason we will monitor the development of immunisation against HLA-antigens, allograft rejection and/or kidney transplant failure following SARS-CoV-2 vaccination.

Considering that items such as mental QoL, anxiety and depression may be positively influenced by vaccination, it is highly relevant to monitor the effect of SARS-CoV-2 vaccination on patient reported outcome measurements (PROMs). In our cohort of dialysis patients PROMs have been monitored since 2019. During the study we will further monitor the course of mental health of vaccinated and non-vaccinated dialysis patients and compare this to pre-COVID-19 pandemic era and the COVID-19 pandemic era without vaccines.

In our study we encountered the challenge to approach a large population to provide informed consent and obtain blood samples under high time pressure. We provided a variety of tools to overcome possible thresholds. First, the digital informed consent gave patients the opportunity to readily access study information and participation. An alternative option to apply for written informed consent was provided, thereby including patients that are not able to access digital platforms. Second by using a home-based finger prick test for antibody measurement, patients were not obliged to make travel expense to obtain blood samples and local health care workers were not burdened with more work during the pandemic. In addition, high-risk patient groups will not be exposed to an additional risk of contamination with SARS-CoV-2 due to extra visits to the hospitals. This strategy may attribute to a higher participation grade.

While our study has a real-life observational design, there are some relevant issues to mention which may impact the results. The reported efficacy depends on the presence of widespread contamination. If for any reason widespread contamination is halted, efficacy of vaccination might be confounded, hence less contamination will occur. The opposite could be the case in the midst of a pandemic where widespread contamination occurs. Additionally, participants are vaccinated according to the national Dutch vaccination programme, in which mRNA-1273 is predominantly administered to high-risk groups, including patients on dialysis or after kidney transplantation. Consequently, certain types of vaccines might be underrepresented. In this study we will only assess the humoral response following SARS-CoV-2 vaccination. Therefore, the immunogenicity of SARS-CoV-2 vaccination in high-risk kidney patients cannot be fully assessed.

Nonetheless, the LESS CoV-2 study will provide key information with regards to the efficacy of SARS-CoV-2 vaccines in high-risk kidney patients. Antibody response data and clinical endpoints will be collected in a large cohort of patients of whom patient characteristics uniformly are obtained in national registries with almost complete coverage. All high-risk kidney patient groups are represented in the study. As such, the study will be sufficiently powered to identify patients’ characteristics and the humoral antibody response predisposing for COVID-19 breakthrough infection. Our study can serve as a template for other studies of vaccine efficacy in high-risk populations including the admission of digital informed consent and finger prick blood sampling at home. Harmonizing the design of vaccination studies will allow international comparison of larger datasets.

## Data Availability

Not applicable.

## Abbreviations

Ab: Antibody
AEs: Adverse Events
BMI: Body Mass Index
CABG: Coronary Arterial Bypass Grafting
CKD: Chronic Kidney Disease
COVID-19: Coronavirus Disease 2019
cPRA: Calculated Panel Reactive Antibody
DSI: Dialysis Symptom Index
eGFR: Estimated Glomerular Filtration Rate
ELISA: Enzyme-Linked ImmunoSorbent Assay
ERACODA: European Renal Association COVID-19 Database
ERA-EDTA: European Renal Association – European Dialysis and Transplant Association
HbA1c: Haemoglobin A1c
HD: Haemodialysis
HIV: Human Immunodeficiency Virus
HLA: Human Leukocyte Antigens
ICU: Intensive Care Unit
IgG: Immunoglobulin G
KRT: Kidney Replacement Therapy
KTx: Kidney Transplantation
LAREB: Netherlands Pharmacovigilance Center
LESS CoV-2: Long term Efficacy and Safety of SARS-CoV-2 vaccination
mRNA: Messenger-RNA
N: Nucleocapsid
NFN: Dutch Federation of Nephrology
NOTR: Dutch kidney transplant recipient registration
NP: Nucleocapsid Protein
NTV: Dutch Transplant Society
NVN: Dutch Kidney Patient Association
PCI: Percutaneous Coronary Intervention
PD: Peritoneal Dialysis
PROMs: Patient-Reported Outcome Measures
QoL: Quality of Life
QR-code: Quick Response code
RBD: Receptor Binding Domain
RECOVAC: REnal patients COvid-19 VACcination
RENINE: Dutch dialysis patient registration
RIVM: Dutch National Institute for Public Health and the Environment
SAEs: Serious Adverse Events
SARS-CoV-2: Severe Acute Respiratory Syndrome Coronavirus-2
S: Spike
SD: Standard Deviation
SF-12: 12-item Short Form Health Survey 12
S1: Spike protein subunit 1
WMA: World Medical Association
WMO: World Medicine Organisation
ZonMw: The Netherlands Organisation for Health Research and Development
